**Figure 6 figure6:**
[figure not shown]
Biomarkers data flow and management from clinical centers to blood-essay evaluation center. ELISA: enzyme-linked immunosorbent assay; qRT-PCR: real-time quantitative reverse transcription polymerase chain reaction.

**Table 2 table2:** Blood-based biomarkers.

Biomarker	Method of measurement
Vitamin D	ELISA^a^
Lutein zeaxanthin	ELISA
Troponin T	ELISA
Pro-brain natriuretic peptide	ELISA
Soluble receptor for advanced glycation end products	ELISA
MicroRNA 125	qRT-PCR^b^
MicroRNA 194	qRT-PCR
MicroRNA 454	qRT-PCR
Interleukin-6	ELISA and Luminex
P16^INK4A^	qRT-PCR
P21^CIP^	qRT-PCR
New unpublished	qRT-PCR and ELISA

^a^ELISA: enzyme-linked immunosorbent assay.

^b^qRT-PCR: real-time quantitative reverse transcription polymerase chain reaction.

### Statistical Analysis

The study population will be characterized based on demographic and clinical attributes. Categorical data will be summarized with frequency and percentage representations. Continuous data will be described using mean, SD, median, and the 25th and 75th percentiles. Furthermore, the distribution of ultrasound parameters with respect to the primary endpoint will be depicted using graphical techniques. The correlation of quantitative biomarkers will be evaluated for each multifactorial clinical evaluation parameter using the Pearson correlation coefficient for continuous variables and the Spearman correlation coefficient for categorical variables [88]. Unpaired tests, such as the Student *t* test, will be used for comparing means of biomarkers among various acquired patient cohorts and for stratified patient subgroups based on the frailty scales outlined in Textbox 1. To manage the extensive array of ultrasound and blood biomarkers, a robust statistical analysis plan will be implemented. This plan will incorporate correction methods to address the risk of type I errors associated with multiple comparisons. Specifically, for the primary outcome concerning biomarker-clinical associations, we will use Lasso regression. This technique automates the selection of relevant variables, reducing the necessity for extensive corrections and improving interpretability. Paired statistics will be applied in the statistical analysis for longitudinal monitoring, encompassing both interventions and clinical follow-up. The monitoring period in hospital and primary care environments will differ to accommodate the distinct follow-up workflows in each setting. The duration of primary care follow-up aligns with established norms [89,90]. To account for differences in follow-up duration among cohorts over time, our data analysis will incorporate appropriate statistical methods, potentially enabling adjustments for these variations. For the secondary objective, the impact of physical intervention in 50 patients will be compared with 50 patients with no intervention. With 80% power, the planned population size will enable the detection of a biomarker with a medium effect size of E/S=0.284 at a 2-sided α level of .05.

In the context of multiparametric data science models, unsupervised learning techniques will be assessed to cluster patient populations based on biomarker expression. Moreover, supervised multi-omics models will be trained using a training set of clinical variables. Stratified cross-validation will be used to derive model performance statistics, ensuring separate patient data in the training and validation folds and maintaining a balanced distribution of health participants and those with frailty in both training and validation sets. Consecutively, sample imputation will be used to address missing data in the training set, while missing reference variables will be excluded during validation and testing. Sensitivity analyses will be conducted to evaluate the impact of the imputation method on the robustness of our results. Reserve data sets, comprising data from various sites and follow-up examinations, will be used for model testing.

Biomarker reproducibility will be evaluated using the interclass correlation coefficient and the Bland-Altmann method, taking into account repeated measurements within an examination. Subgroup analyses will be conducted to explore variations across patient subpopulations, and regression models will be used to examine the influence of covariates, thereby enhancing methodological precision.

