### Randomization and Blinding

Data analysis will be conducted independently of cohort recruitment and follow-up. The evaluation of data will take place at the Deusto Institute of Technology (Ultrasound Data Evaluation Center) and Biodonostia (Blood-based Assays Evaluation Center). Initially, only anonymized data, including ultrasound images, raw data, and blood-based assays, will be transmitted to the data evaluation centers. In the case of combination models, a training set of clinical variables will also be transferred to the data evaluation centers. Reserved data sets will be kept at the clinical acquisition centers for independent testing. This includes data from various sites and information obtained during follow-up examinations.

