#### Secondary Outcomes

In the hospital exercise cohort, we will assess changes in quantitative ultrasound and blood-based biomarkers, as well as clinical variables, following a 16-week multicomponent physical exercise program. Additionally, exploring associations between ultrasound and blood-based biomarkers and the remaining clinical variables both before and after the exercise program.In the hospital control cohort, we will examine changes in quantitative ultrasound and blood-based biomarkers, along with clinical variables, following a 16-week follow-up period without intervention. Furthermore, we will explore associations between quantitative ultrasound and blood-based biomarkers and the remaining clinical variables after the 16-week follow-up period.In the primary care cohort, we will assess changes in quantitative ultrasound and blood-based biomarkers, along with clinical variables, following a 1-year follow-up period without intervention. Additionally, we will explore associations between quantitative ultrasound and blood-based biomarkers and the remaining clinical variables after the 1-year follow-up.We will evaluate differences in the changes of all measurements among the 3 cohorts. A direct comparison will be made between the 2 hospital cohorts, while the primary care cohort will serve as a reference for understanding changes in nonhospital populations.

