#### Raw Data Evaluation

Quantitative ultrasound biomarkers will be assessed offline using the acquired raw IQ data. Regions of interest encompassing the rectus femoris will be delineated in the raw data domain by automatically generating B-mode images from the raw data. This process will use the coregistered clinical B-mode images and sonographer annotations as a reference for the definition of the accurate region of interest. Table 1 presents a list of state-of-the-art quantitative ultrasound biomarkers, the hyperparameters of which will be systematically adjusted through experimental adaptation for musculoskeletal examinations. These adjustments will be made and subsequently evaluated using the raw data obtained from the ultrasound probes during the study.

**Table 1 table1:** Quantitative ultrasound biomarkers based on raw data.

Biomarker	Description	Literature references
Automatic morphometric measurements	Automatic muscle morphometric analysis based on neural network segmentation models trained with respect to sonographer annotations of rectus femoris cross section, and 2D Fourier analysis of pennation angle.	[72,73]
Attenuation coefficient	Measurement of loss of signal intensity with depth.	[47,48,50]
Backscattering coefficient	Measurement of tissue reflectivity after attenuation compensation.	[74,75]
Power spectrum (Lizzi-Feleppa parameters)	Spectroscopy measurement of backscattered signal variation with frequency, including parametrizations such as spectral slope, spectral intercept, and midband fit	[49]
Speckle statistics	Fitting of raw envelope signal to speckle statistical distribution models, including Rayleigh, Nakagami, and homodyned K-distribution. Estimation of scatterer concentration, spacing, and coherence from fitted model parameters.	[49,76,77]
Statistical moments	Nonparametric statistical moments capturing scatterer distribution and concentration, such as entropy, kurtosis, skewness, variance, anisotropy, and signal-to-noise ratio.	[78,79]
Coherence and speed of sound	Generalized spectrum analysis and estimation of coherence, mean scatterer spacing, and speed-of-sound in muscle.	[80,81]
Textural radiomics	First- and second-order texture features extracted from both B-mode (eg, based on gray-scale co-occurrence matrices) and raw data (eg, based on wavelet and Laplacian transformations) and combined with machine learning models trained with respect to clinical outcomes.	[51,53,54]

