Artificial intelligence radiomics	Radiofrequency data and B-mode features extracted automatically with end-to-end neural network models trained with respect to clinical outcomes	[52,82-84]

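### Paired change in outcome-trained scores can show a false shift, because baseline examinations train the model while follow-up examinations are reserved

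*Protocol article*

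**What the plan says.** Table 1 (Methods, Raw Data Evaluation) lists nine families of quantitative ultrasound biomarkers. Two are fitted to clinical outcomes. Textural radiomics features are "combined with machine learning models trained with respect to clinical outcomes", and artificial intelligence radiomics uses "end-to-end neural network models trained with respect to clinical outcomes". The Statistical Analysis section adds supervised multi-omics models trained on clinical variables.

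On the data kept out of training, Randomization and Blinding says: "This includes data from various sites and information obtained during follow-up examinations". Statistical Analysis repeats it: "Reserve data sets, comprising data from various sites and follow-up examinations, will be used for model testing". Training therefore uses baseline examinations. The reserved sites are not named.

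Change is a secondary outcome. In the exercise cohort, "we will assess changes in quantitative ultrasound and blood-based biomarkers, as well as clinical variables, following a 16-week multicomponent physical exercise program"; similar wording covers the other two cohorts, and the two hospital cohorts are to be compared directly. The method is: "Paired statistics will be applied in the statistical analysis for longitudinal monitoring, encompassing both interventions and clinical follow-up".

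Cross-validation is planned "ensuring separate patient data in the training and validation folds", but its stated purpose is to obtain model performance statistics. The protocol does not say which model produces the scores that enter the change tests.

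**The concern.** A model fitted to a participant's baseline label carries some of that participant's own noise. This own-fit part is fully present when the same baseline is scored, and only partly present at follow-up. Subtracting the two visits can then turn overfitting into change.

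The effect need not average out, because the Sample Size section expects 85% frail in the hospital cohorts and 15% in primary care. In a pooled model the own-fit part pushes the two settings in opposite directions. A spurious shift in the exercise cohort could be read as a training response, and one in primary care as ageing or recovery. This matters because the Discussion (Principal Findings) expects the advanced models to be more responsive to change in muscle quality than the simple geometric measures.

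**Working it through.** The plan gives no figure on this point to reproduce. It supplies cohort sizes (50 exercise, 50 control, 100 primary care) and the frailty mix (85%, 85%, 15%). The same section's projection of 139 robust and 86 frail participants does not follow from that mix, so the percentages are used here.

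**Step 1: the mechanism.** Let ρ be the between-visit repeatability of the features, and let A be the own-fit part of a training participant's baseline score. A model fitted on baseline retains about ρA of it at follow-up. With no true change, the expected change is:

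- in-sample baseline, same model at follow-up: ρA − A = −(1 − ρ)A
- out-of-fold baseline, full model at follow-up: ρA − 0 = +ρA
- both visits scored by one model that excluded the participant: 0

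**Step 2: the cohort mean of A.** With weak features this is roughly proportional to cohort frailty minus training-set frailty.

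- All cohorts pooled: training frailty = (0.85 × 100 + 0.15 × 100)/200 = 0.50. Hospital: 0.85 − 0.50 = +0.35. Primary care: 0.15 − 0.50 = −0.35. The shifts are equal and opposite.
- One setting only: the difference is 0, so there is no mean shift.
- One hospital plus primary care: training frailty = (42.5 + 15)/150 = 0.383. Trained hospital: +0.467. Primary care: −0.233. Reserved hospital: A = 0, because neither visit belongs to a training participant.

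**Step 3: simulation with no true change.** Ridge score trained on baseline frailty; 100 to 150 runs per setting; two-sided paired t test at 0.05. Assumed, not in the protocol: the number of features (5 of them informative, at 0.5 SD), the repeatability and the penalty (cross-validated here). Monte Carlo standard error with 100 runs is √(0.05 × 0.95/100) = 0.022 at 5%, and 0.05 at 50%. Negative means apparent improvement. Order: exercise / control / primary care, pooled training.

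| Features | ρ | Scoring | Mean change | Rejection rate |
|---|---|---|---|---|
| 200 | 0.5 | in-sample baseline | −0.033 / −0.033 / +0.034 | 0.48 / 0.56 / 0.85 |
| 200 | 0.8 | in-sample baseline | −0.014 / −0.015 / +0.016 | 0.26 / 0.26 / 0.50 |
| 200 | 0.95 | in-sample baseline | −0.003 / −0.004 / +0.003 | 0.08 / 0.07 / 0.15 |
| 50 | ≥ 0.8 | in-sample baseline | – | 0.03 to 0.09 |
| 1000 | 0.8 | in-sample baseline | −0.024 / −0.023 / +0.024 | 0.82 / 0.85 / 0.99 |
| 200 | 0.8 | out-of-fold baseline, full model at follow-up | +0.062 / +0.059 / −0.061 | 0.95 / 0.97 / 1.00 |
| 1000 | 0.8 | out-of-fold baseline, full model at follow-up | +0.097 / +0.096 / −0.095 | 1.00 / 1.00 / 1.00 |
| 1000 | 0.8 | one model without the participant, both visits | 0.000 / 0.000 / +0.001 | 0.06 / 0.07 / 0.06 |

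The simulation agrees with Step 1. With 1000 features and ρ = 0.8, A in the exercise cohort is 0.024 + 0.097 = 0.121, so −(0.2)(0.121) = −0.024 and +(0.8)(0.121) = +0.097.

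**Step 4: exercise versus control.** With both hospitals in training, rejection was about 0.05. With one hospital reserved and the other trained with primary care (200 features, ρ = 0.8), it was 0.33 to 0.35 with in-sample baselines and 0.99 to 1.00 with mixed scoring. A weaker penalty gave 0.15 to 0.17 and 0.76 to 0.81. Training on one setting only gave rates no higher than about nominal.

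**Step 5: with the fix.** Scoring both visits by one model that excluded the participant gave rejection rates of 0.00 to 0.09 across the pooled settings, with mean change about 0.

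**The case against.** The strongest reply is that the protocol nowhere says in-sample baseline scores enter the paired tests. It plans patient-separated cross-validation and reserves whole sites, both of which can supply clean scores, and the choice of scoring model is ordinary analysis-plan detail. It stands that in-sample scoring is an inference. It does not settle the matter, because the article itself fixes a split by visit within the same person and then tests the difference between those visits. Cross-validation is tied to performance statistics only. If it were used for baseline alone, the error would be larger, not smaller.

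A second reply is scope. Seven of the nine Table 1 families are not trained on clinical outcomes. Primary Outcomes describes the ultrasound biomarkers by thickness, area, perimeter and pennation angle, and Secondary Outcomes names no trained score. This stands as a limit: the point covers only outcome-trained scores. That such scores will be tested for change is a reading of Table 1 together with the Discussion, though a natural one.

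A third reply is that at least 12 frames per examination should make features repeatable, which shrinks the in-sample artefact. That is fair in part. The quantity that matters, however, is repeatability across 16 weeks or a year, while the planned reproducibility analysis uses repeats within one examination.

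Pooled training is also not stated. The balanced mix of healthy and frail participants wanted in the folds fits pooling better than single-setting training, but does not prove it.

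**Conclusion.** The point holds conditionally. For textural radiomics, artificial intelligence radiomics and supervised multi-omics scores, the plan leaves paired change open to a train/test asymmetry whose sign and size depend on unstated choices. If training pools hospital and primary care, in-sample baselines give false improvement in hospital and false decline in primary care. Out-of-fold baselines with full-model follow-up reverse both.

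With in-sample baselines, a cross-validated penalty, 50 or 200 features and repeatability of at least 0.8, paired false-positive rates ran from near nominal to about 50%. They were higher with 1000 features or lower repeatability, and higher again with mixed scoring at repeatability 0.8 and above. These are ranges under assumed settings, not predictions.

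A reader might infer more, but the documents do not support it:

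- That hospital patients will falsely improve. The direction is not fixed, and the mean shift is absent if training uses one setting.
- That the exercise-versus-control contrast is biased. It is protected if both hospitals train. It is biased if one is reserved while the other trains with primary care, and the reserved sites are not named.
- That a separate test set offers no protection. Participants at sites wholly reserved from training have neither visit in the fit and are unaffected.

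**What to change.** Add to Statistical Analysis: *For every score trained on clinical outcomes, both visits of a participant are scored by the same model, fitted without any examination of that participant (the models from the patient-separated cross-validation, or a model trained at other sites). Paired and between-cohort tests of change use only these scores.*

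No new data are needed. The patient-separated cross-validation is already planned, so the cost is re-scoring stored examinations. The drawback is that each score comes from a model fitted on slightly fewer participants.

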### Ethical Considerations

This study protocol received approval from the Research Ethics Committee of Albacete (Spain) with reference CEIm-2021-51. The study will be conducted in adherence to the principles outlined in the Declaration of Helsinki [91]. Before participation, written informed consent will be obtained from all participants, and their data will be handled in accordance with HIPAA guidelines. Additionally, consent will be sought for the review of participants’ medical records and for the collection of blood samples to assess biomarkers. In the event of necessary modifications to this protocol during the clinical research, the changes will undergo review by the hospital ethics committee and will be implemented only after obtaining approval. The trial results will be communicated to participants via email by the investigators. Participants involved in this study will not receive any form of compensation for their participation.

The study information will be stored in Microsoft Excel 365 within an electronic database. This database will comprehensively capture individual data, including baseline characteristics, pre- and postassessment data, and any potential adverse events. Notably, no personally identifiable patient information, apart from the unique trial identification number, will be included in the metadata associated with the recorded ultrasound and biomarker data. Ultrasound and biomarker data will be uploaded to a HIPAA-compliant cloud service provided by the ultrasound system manufacturer, enabling centralized evaluation by team members. As outlined in the reference manuscript, upon completion of the study, digitized data sets encompassing ultrasound data, biomarkers, digitized blood-based biomarkers, and anonymized multifactorial clinical evaluations will be published in open-access repositories, such as Zenodo (CERN). Biological samples will be securely stored in the Basque Biomarker Center (Biobanco). Additionally, software models derived from ultrasound raw data will be made accessible through open-source software repositories (eg, GitLab).

## Results

The initial analysis results indicate a correlation between ultrasound morphometric parameters and clinical variables (Table 3). This table examines the correlations of ultrasound geometric parameters with clinical variables. The clinical data considered in this analysis are derived from a subset of the hospital cohort, comprising a total of 66 participants. Specifically, correlations between clinical variables and ultrasound parameters during the basal examination have been included in the table.

**Table 3 table3:** Preliminary correlations at baseline visit for the hospital cohort (n=66).

Correlations	Thickness run average, *r* (*P* value)	Area run average, *r* (*P* value)	Angle run average, *r* (*P* value)
Age	–0.023 (.82)	0.002 (.98)	–0.072 (.47)
BMI	0.269 (.009)^a,b^	–0.016 (.88)	0.167 (.09)
Charlson	–0.180 (.09)	–0.213 (.04)^a,b^	–0.018 (.85)
Barthel Index	0.058 (.58)	0.176 (.09)	0.224 (.02)^a,b^
Lawton and Brody Index	–0.002 (.98)	–0.056 (.60)	0.220 (.02)^a,b^
Mini Nutritional Assessment—Short Form	0.183 (.08)	0.036 (.74)	0.210 (.03)^a,b^
SARC-F^c^	–0.098 (.35)	–0.236 (.02)^a,b^	–0.158 (.11)
Grip strength	0.240 (.02)^a,b^	0.372 (<.001)^a,b^	0.105 (.32)
Short Physical Performance Battery total	0.288 (.005)^a,b^	0.355 (.001)^a,b^	0.197 (.04)^a,b^
Gait speed	0.168 (.11)	0.327 (.002)^a,b^	0.241 (.01)^a,b^
Frailty phenotype (Fried et al [4])	–0.101 (.34)	–0.211 (.04)^a,b^	–0.044 (.68)
FRAIL^d^	–0.125 (.24)	–0.284 (.006)^a,b^	–0.034 (.73)
DXA^e^ total muscle mass	0.473 (<.001)^b,f^	0.498 (<.001)^b,f^	0.143 (.28)
DXA ALM^g^	0.440 (<.001)^b,f^	0.539 (<.001)^b,f^	0.100 (.45)
DXA ALM/h^2^	0.529 (<.001)^b,f^	0.493 (<.001)^b,f^	0.115 (.38)
DXA total fat	0.271 (.04)^a,b^	0.29 (.83)	0.130 (.32)
DXA fat percentage	0.132 (.31)	–0.239 (.07)	0.064 (.63)

^a^Significant weak correlations (*r*<0.4).

^b^Significant correlations (*P*<.05).

^c^SARC-F: Strength, Assistance with walking, Rising from a chair, Climbing stairs, and Falls.

^d^FRAIL: short 5-question assessment of Fatigue, Resistance, Aerobic capacity, Illnesses, and Loss of weight.

^e^DXA: dual-energy X-ray absorptiometry.

^f^Significant moderate and strong correlations (*r*>0.4).

^g^ALM: appendicular lean soft tissue mass.

The analysis revealed significant moderate correlations between muscle cross-section and thickness and DXA parameters (Table 3). Notably, the highest correlation (*r*=0.539, *P*<.001) was observed between DXA appendicular mass and muscle cross section. Additionally, significant weak correlations were identified between functional variables (such as gait speed, grip strength, and SPPB) and ultrasound morphometric parameters (including muscle section, thickness, and pennation angle; indicated in Table 3 in rows 7, 8, and 9, respectively). The frailty scale (FRAIL, Fried et al [4]) and the sarcopenia scale (SARC-F) exhibited weak but significant associations with muscle cross section as illustrated in row 2 of Table 3. Additionally, significant weak correlations were identified between pennation angle and measures of independence (Barthel and Lawton Index) as well as nutritional assessment (Mini Nutritional Assessment—Short Form) as detailed in Table 3. Notably, age did not demonstrate a significant association with ultrasound morphometric variables (*r*=–0.023, *P*=.82; *r*=0.002, *P*=.98; and *r*=–0.072, *P*=.47, respectively). However, a weak correlation was observed between BMI and muscle thickness.

